### Study aims

RESCUE + PE will decrease emotional-numbing symptoms of PTSD relative to the PE control arm (CI + PE) primary outcomeRESCUE+PE will be feasible and acceptable to veteransTreatment engagement will be higher for the RESCUE + PE group relative to CI + PE group (i.e., higher treatment attendance rates (primary), homework completion rates, and treatment completion rates)Treatment recovery rates (as measured by PTSD diagnostic status yes/no; decreased PTSD symptom severity; and increased quality of life) will be higher for the RESCUE + PE group compared to the CI + PE group at post treatment and at 3-month follow-upParticipants randomized to RESCUE + PE will experience a decrease in PTSD numbing from pre to post treatment relative to those randomized to CI + PI

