### Randomization procedures

Once eligibility is established, veterans are assigned 1:1 to one of the two treatment groups by the Project Coordinator using a web-based computer-generated randomization scheme. Once a veteran is randomized and attends the first session, they are entered into the study and included in the intent-to-treat (ITT) analysis. The post-treatment assessors (12- and 3-month assessors) will be blinded to condition. The Principal Investigator (PI) (for clinical oversight/supervision) and Project Coordinator (for randomization/regulatory reasons) will not be blinded to treatment condition. The study therapists likewise will not be blinded because discussion of volunteer assignments is part of the treatment protocol. It is not anticipated that the post-treatment assessors will need to be unblinded as this will be their only point of contact with the study participant. If the blind is accidentally broken, the Clinician Administered PTSD Scale (described below) will be reviewed by another team member for fidelity and evaluated against the PTSD Symptom Checklist (described below) which is self-report.

Inclusion criteria for the study are as follows: (1) *Diagnostic and Statistical Manual for Mental Disorders, version 5* (DSM-V) PTSD diagnosis (via the Clinician Administered PTSD Scale; CAPS [22];) stemming from a duty-related Criterion A event [23]; (2) male or female aged 18 to 64 years.

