### Sample size calculation and power analyses

For the continuous longitudinal clinical, functional, and process outcomes for Primary Aims, with 35 subjects randomized to each intervention group, we will have 85% power to detect at least a 0.3 standardized (sd units) effect size between the two intervention groups assuming three time points, and an intra-class correlation no greater than 0.5; level of significance ≤ 0.05, two-tailed. A standardized effect size of 0.35 sd (Cohen’s *d*, “small” effect) is equivalent to a raw effect size of 2.8 raw scale units for the PCL (assuming pooled sd for post-treatment PCL scores is 8.1, from preliminary data). All participants randomized to condition and having completed a baseline assessment will be included in ITT analyses.

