### Analytic strategy

Data screening for violations of proposed statistical methods assumptions (normality of endogenous variables, linear relations among variables, no outliers, limited missing data/appropriate method for handling missing data) will include histograms, bivariate correlations, Q-Q plots, and other diagnostic methods. Processes associated with subject attrition will be examined to determine whether a missing-at-random assumption is defensible. Data will be analyzed to determine whether missing values are correlated with any baseline values and all relevant psychometric variables will be examined between groups at the baseline point of measurement to ensure adequate randomization. Given limitations of last-observation-carried-forward (LOCF), hierarchical linear models (HLM)/mixed models will be used for ITT analyses of primary and secondary outcome variables. Statistically significant treatment-related changes will be qualified with effect-size estimation and 95% confidence interval estimation.

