### Treatment effects

Treatment effects will be examined via changes on continuous measures of PTSD numbing symptoms from the CAPS-5, PCL-5, and ERNS as well as by changes on continuous CAPS-5 and PCL-5 total scores, other associated mental health outcomes (e.g., BAI, PHQ-9), and functional status/quality of life (e.g., WHODAS-II; QLI). CAPS-5 and PCL-5 emotional-numbing items will be analyzed separately based on factor analytic findings and the current hypothesis that RESCUE will specifically decrease emotional-numbing symptoms.

To evaluate pre-post treatment continuous outcome measures, HLM/mixed models will be estimated with randomized group entered as a level-2 fixed effect. Effect sizes and 95% confidence intervals will be employed in a manner consistent with accepted norms [35]. For multiple point measurement related to self-report measures, estimates of slope will also be tested. For dichotomous outcomes, rates will be assessed by chi-square comparison of between-group percentages. Diagnostic improvements will be examined by computing the percentage of treated participants who no longer meet PTSD criteria at each follow-up. Outcomes will also be evaluated using CGI-I scores at all post-treatment follow-ups (i.e., percentage of veterans receiving a CGI-I rating of 1 or 2).

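### Loss of PTSD diagnosis is computed among undefined treated participants, which conflicts with the all-randomised ITT rule and conditions on an event the trial expects to differ by arm

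*Protocol article*

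**What the plan says.** The statements that bear on this are all in the protocol article.

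- **Study aims** makes remission a between-group hypothesis at post treatment and at 3 months: "Treatment recovery rates (as measured by PTSD diagnostic status yes/no" is the first component of the recovery aim. The same list hypothesises higher attendance, homework completion and treatment completion with RESCUE + PE.
- **Treatment effects** fixes the remission denominator: "Diagnostic improvements will be examined by computing the percentage of treated participants who no longer meet PTSD criteria at each follow-up". The test is given separately: "For dichotomous outcomes, rates will be assessed by chi-square comparison of between-group percentages".
- **Sample size calculation and power analyses** defines the ITT population: "All participants randomized to condition and having completed a baseline assessment will be included in ITT analyses".
- **Randomization procedures** defines it differently: "Once a veteran is randomized and attends the first session, they are entered into the study and included in the intent-to-treat (ITT) analysis".
- **Analytic strategy** commits, without exception for binary outcomes, that "hierarchical linear models (HLM)/mixed models will be used for ITT analyses of primary and secondary outcome variables", and gives the limitations of LOCF as the reason.
- **Assessment measures** says that veterans who leave treatment early are encouraged to attend follow-up and are paid for it.

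The word *treated* is not defined anywhere.

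**The concern.** A between-group comparison is protected by randomisation only if who is counted does not depend on what happened after assignment. *Treated* describes something that happens after assignment. In many trials the resulting selection would be a modest worry. Here the trial is built on the expectation that RESCUE changes who engages with PE and who stays. If that expectation is right, the treated groups in the two arms differ in composition as well as in size.

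At stake is the diagnostic component of the recovery aim. If RESCUE helps by keeping veterans in PE, a remission percentage among the treated can show no gain. If the veterans it keeps respond less well than those who would have stayed anyway, the percentage can turn against RESCUE. The Discussion says attention should go to engagement and retention rather than to outcomes among those who comply. A percentage of the treated tends to measure the latter.

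The chi-square adds a second, smaller difficulty. Run on raw percentages it has no means of dealing with a missing diagnosis, although the Analytic strategy section chose mixed models for the ITT analyses on missing-data grounds.

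**Working it through.** **Plan's own figure.** There is none to reproduce. The plan states no expected rate, sample size or power for any dichotomous outcome; its 85% power figure concerns continuous longitudinal outcomes and does not bear on this point.

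**Step 1: the two readings of *treated*.**

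- *Completed PE.* The denominator is selected on completion, which Study aims hypothesises to differ by arm. It conflicts with both ITT definitions.
- *Attended at least one session.* This agrees with the Randomization procedures section but conflicts with the sample size section, because randomised veterans with a baseline who never start are left out. Assignment precedes session 1, and the section on RESCUE says staff go over the volunteer expectations before treatment starts. Starting can therefore depend on the arm.

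Both readings condition on a post-randomisation event, and both conflict with the all-randomised rule.

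**Step 2: what a completer denominator can do.** This is an illustration on assumed rates. Let d_C and d_R be dropout in CI + PE and RESCUE + PE. Let p_c be remission in veterans who would complete in either arm, p_d remission in dropouts, and p_m remission in the extra veterans whom RESCUE retains. RESCUE is assumed to act only through retention, and every veteran's diagnosis is taken as known.

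- All randomised, CI: (1 - d_C)p_c + d_C p_d
- All randomised, RESCUE: (1 - d_C)p_c + (d_C - d_R)p_m + d_R p_d
- All-randomised difference: (d_C - d_R)(p_m - p_d)
- Completer difference: (d_C - d_R)(p_m - p_c) / (1 - d_R)

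Inputs:

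- d_C = 0.36, the pooled dropout rate cited in the Background.
- p_c = 0.80, borrowed from the Background. That figure is clinically meaningful improvement in completers, not loss of diagnosis.
- d_R = 0.16 and p_d = 0.10, pure assumptions.

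CI, all randomised: 0.64 × 0.80 + 0.36 × 0.10 = 0.548.

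| p_m | RESCUE, all randomised | All-randomised difference | Completer difference |
|---|---|---|---|
| 0.80 | 0.512 + 0.160 + 0.016 = 0.688 | 0.20 × 0.70 = +14.0 points | 0.20 × 0 / 0.84 = 0.0 |
| 0.40 | 0.512 + 0.080 + 0.016 = 0.608 | 0.20 × 0.30 = +6.0 points | 0.20 × (-0.40) / 0.84 = -9.5 points |
| 0.10 | 0.512 + 0.020 + 0.016 = 0.548 | 0.20 × 0 = 0.0 | 0.20 × (-0.70) / 0.84 = -16.7 points |

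Row one is a real benefit that disappears, row two a real benefit that reverses, and row three no effect that looks like harm. Whenever p_m lies between p_d and p_c and RESCUE retains more veterans, the first difference cannot be negative and the second cannot be positive.

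Varying the assumptions (completer remission 60% or 80%, dropout remission 10% or 20%, RESCUE dropout 16% to 36%) gives all-randomised differences of 0 to +14.0 points and completer differences of 0 to -16.7 points. If RESCUE retained fewer veterans, the bias would run the other way.

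**Step 3: the first-session reading.** The same algebra applies with never starting in place of dropping out. The document gives no arm-specific rate of never starting after randomisation, so no figure can be attached.

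**The case against.** The strongest defence is that *treated* means attended the first session. Everyone in the ITT set of the Randomization procedures section has been treated in that sense, so the remission sentence would follow one of the trial's own definitions. That is a fair reading, and a reader who infers a completers-only analysis goes further than the text. It does not clear the point: that set still omits randomised non-starters, whom the sample size section includes.

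Second, a general statement on mixed models followed by a specific one on chi-square is ordinary drafting. Chi-square is a test and ITT is an analysis set, and the one can be run on the other. This is correct. The chi-square is a departure from the mixed-model commitment, not in itself a breach of ITT. Leaving out baseline severity costs precision and is not a bias.

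Third, veterans who drop out of treatment may still be assessed, the plan examines attrition, and an unseen analysis plan may deal with missing binary data. All of this reduces the missing-data concern. It does not touch the denominator, which the article itself states.

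Fourth, diagnostic status is not labelled primary. Engagement has its own outcomes, and severity and quality of life go through mixed models. This limits the importance of the point but does not remove it.

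Two stronger inferences are tempting and not supported:

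- *That all yes/no outcomes are restricted to the treated.* The chi-square sentence names no denominator, and the CGI-I sentence refers to the "percentage of veterans receiving a CGI-I rating of 1 or 2". Treatment completion is not restricted either.
- *That a fixed number of points is being hidden.* Suppose 28/35 and 22/35 are assessed and half of each remit. The observed rates are 14/28 and 11/22, both 50%, and counting missing as not remitted gives 14/35 = 40.0% against 11/35 = 31.4%, a gap of 8.6 points. That gap comes wholly from the counting rule, and it treats the 36% treatment dropout as assessment loss. Without further information a missing-at-random analysis would also return about 50% in each arm.

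**Conclusion.** The concern holds for loss of PTSD diagnosis. The article states a remission denominator that conflicts with its own all-randomised ITT rule and, on either reading of *treated*, depends on a post-randomisation event in a trial that hypothesises a difference in engagement. The comparison can be biased and can miss or reverse a benefit acting through retention. The conclusion rests on the wording and on the engagement hypothesis, not on the illustrated rates. The actual size cannot be derived from the document: it depends on what *treated* means, on how far the arms differ in starting or staying, and on how many dropouts are assessed. The point does not extend to CGI-I response or treatment completion. It should be corrected; it does not affect the outcome that the aims name as primary, emotional numbing.

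**What to change.** 1. Define one ITT set and use it in the Randomization procedures, Sample size and Treatment effects sections. All randomised veterans with a completed baseline, as the sample size section already says, is the natural choice.
2. Use that set as the denominator for loss of diagnosis at post treatment and at 3 months, in place of *treated participants*.
3. Handle missing diagnostic status by multiple imputation using baseline CAPS-5 and the weekly PCL-5, or by a logistic mixed model. Report the risk difference with its 95% CI.
4. Add missing-as-not-remitted as a sensitivity analysis.
5. Keep chi-square for fully observed outcomes such as treatment completion, on all randomised.

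Imputation does not replace follow-up of veterans who leave treatment. It can recover a retention effect only as far as their assessments or their PCL-5 scores before leaving carry the information.

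The cost is a revised paragraph and a little more analysis work. No new data are needed, since the baseline CAPS-5 and weekly PCL-5 are already collected.

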### Dissemination of study findings

The study team will conduct dissemination activities throughout the project period— both locally within the Charleston VA, in informal presentations to other southeastern VA hospitals, and across the country at professional conferences. We will also use our own core and extended collaborative relationships to distribute information. Specifically, dissemination activities will include (1) authorship of descriptive materials that outline the study and its objectives in the form of white papers and brochures; (2) publication of the study results in professional and non-professional outlets, such as psychiatric and medical journals; (3) presentations and lectures in the form of graduate courses on treatment outcome research, seminars on innovations in treatment, invited grand rounds at our respective and other Universities, meetings describing project results; (4) active, ongoing evaluation of these activities; and (5) distribution of summary data to relevant stakeholders, including VA National Centers for PTSD (i.e., the PTSD Mentoring Program and the Practice Based Implementation Network), DoD, and other VAMCs.

The study PI will record and track all dissemination activities and direct project Co-Is and other study personnel to increase or widen the scope and frequency of these activities when appropriate. She will also actively participate in the majority of these activities herself. The PI will coordinate the data analysis for the project, relevant manuscript submissions, presentations, mailings and other forms of distribution, publicity, etc. The PI and Co-Is will author all manuscripts related to the project (i.e., no professional writers will be used). The PI will also guide dissemination efforts through the national programs described above. No more than 3 years after the collection of the 3-month post-assessment interviews, the PI will provide a de-identified dataset to an appropriate data archive for sharing purposes. The study protocol will be available upon request within 6 months of the study end date.

## Discussion

Despite systemic efforts by the DoD and VA to ensure that EBTs are available to all veterans with PTSD, many veterans are not initiating or completing treatment. This is a significant issue given that PTSD does not typically remit over time and is associated with significant impairment across a range of psychosocial indices. Given the increased availability of EBTs, and the well documented and robust effect sizes for patients who complete PE, more attention should be given to testing novel methods for improving treatment engagement and retention rather than further improving outcomes among those who comply with PE treatment guidelines. As with other psychiatric disorders (e.g., depression), the symptoms that pose as a barrier to treatment engagement should be targeted directly to improve treatment initiation, engagement, and completion [36]. In this effort, the current clinical trial focuses on addressing the emotionally numbing symptoms of PTSD using a HAI model.

In addition to being part of the symptom profile of PTSD, emotional numbing can serve as a barrier to care through its heightened association with apathy, low motivation, and feeling disconnected from others [10, 14]. Unfortunately, current EBTs do not target emotional numbing directly. Thus, although emotional-numbing symptoms can decrease with treatment of a sufficient duration, targeting them proactively and effectively in the early stages of treatment is likely to improve overall treatment retention and subsequent clinical improvement. Based on the broader HAI literature, RESCUE (the experimental condition) was designed explicitly as an adjunctive therapy to augment extant EBTs by decreasing emotional-numbing symptoms, increasing veteran “buy in,” facilitating avenues for effective EBT psycho-education, and increasing supportive and therapeutic in-vivo exposure and commensurate behavioral activation, thereby improving PTSD EBT engagement and completion rates.

A strength of the proposed project is that it is designed to target the significant number of veterans and active duty personnel with PTSD who are at risk for refusing or dropping out of EBTs [4, 5, 7, 37]. Additionally, RESCUE incorporates HAI into the chronological treatment progression of PE by taking advantage of an already existing and disseminated infrastructure related to (1) volunteering at an SPCA to socialize shelter dogs for eventual adoption and (2) standard PTSD treatment guidelines (i.e., in-vivo exposures) as mandated by the Uniform Mental Health Services Handbook (VHA HANDBOOK 1160.01). By taking advantage of the availability of SPCA shelters nationally as well as existing service delivery models for PTSD, RESCUE can easily be scaled up for wide-scale implementation and dissemination. Further, the theory-driven mixed quantitative/qualitative methods design of this trial will allow for a better understanding of how HAI may be beneficial for individuals with PTSD as well as provide information on how to further improve the treatment program moving forward. Altogether, this study should provide timely information regarding incorporating HAI into EBTs for PTSD.

A significant contribution of the current study is in relation to specifying an ecologically valid, active, and well-matched control condition designed to determine animal-specific or HAI-specific effects. Additionally, much of the extant literature to date has focused on the beneficial health effects of HAI through long-term pet ownership rather than the effects of specific interventions. Finally, reviews of HAI specifically related to therapeutic interventions or specific clinical populations suggest an overall lack of methodological rigor [16, 18–20] which is a considerable barrier to progress in the field. The current study team noted these trends when designing the trial and decidedly erred on the conservative side in relation to specifying the control group. The control group is well matched in and outside of treatment sessions and participants are randomly assigned to conditions. Additionally, the experimental condition is not related to receiving additional services or a service dog, and therapy is provided using an ecologically valid treatment setting and referral stream.

Despite the above study strengths, a few limitations merit note. First, it was not practical or possible to blind the study therapists to condition given the treatment context which necessitated discussion of the volunteer assignment during sessions. However, the current study team’s research focus and experience is related to treating PTSD in VA contexts using exposure-based interventions, and not to HAI. Thus, the potential for implicit bias toward the experimental condition is somewhat mitigated. Second, given that veterans in the CI + PE group can self-select their volunteer activity, factors related to preference, comfort, and scheduling ease (i.e., ease of choosing a volunteer assignment close to home) could obscure potential gains related to RESCUE. The use of both quantitative (i.e., tracking of attendance and discussion of volunteer successes and challenges as part of therapy) and qualitative data (i.e., thematic interviews), however, will allow for a better understanding of the impact of these factors on outcomes. Finally, as is often the case with clinical trials, the current study design is geared to provide more easily interpretable effects given a positive outcome rather than a negative outcome. Although this is important for HAI research at this stage, negative findings will be somewhat more difficult to interpret and would not rule out the potential for other more intense, or more active HAI augmentations to EBTs.

## Implications and conclusions

PTSD is one of the most prevalent mental health disorders among post-deployed veterans [38]. Despite the wide-scale availability of EBTs for PTSD within DoD and VA health care settings, however, a significant number of veterans and active duty personnel fail to initiate treatment or drop out of treatment prematurely before experiencing meaningful symptom relief. The current study is designed to address these barriers to care through RESCUE, a novel adjunct to PE based on findings regarding emotional numbing and HAI therapeutic models. If proven efficacious, RESCUE has the potential to yield significant and meaningful cost savings at the individual level with regard to suffering and lost work productivity as well as at the systems level with regard to disability and health care utilization patterns.

